# Universal Versus Conditional Third Day Follow-Up Visit for Children With Nonsevere Unclassified Fever at the Community Level in Ethiopia: Protocol for a Cluster Randomized Noninferiority Trial

**DOI:** 10.2196/resprot.9780

**Published:** 2018-04-12

**Keywords:** community health workers, Ethiopia, malaria, fever, child

## Abstract

**Background:**

Under the World Health Organization’s integrated community case management strategy, febrile children seen by community health workers (on day 1) without a diagnosable illness and without danger signs are advised to return on day 3, regardless of symptom resolution. This advice might be unnecessary and place additional time and cost burdens on caregivers and community health workers. However, the safety of not following up with respect to children with unclassified fever is unknown.

**Objective:**

The objective of this study is to establish the safety of conditional follow-up of nonsevere unclassified fever, that is, nonsevere illness with fever, no malaria, pneumonia, diarrhea, or danger signs, compared with universal follow-up on day 3, through a 2-arm cluster randomized controlled noninferiority trial.

**Methods:**

The study is being conducted in 3 districts in southwest Ethiopia. A total of 25 health facilities are randomized to one of the 2 intervention arms; all 144 health posts and 284 community health workers are included. All enrolled children are followed-up after 1 week (on day 8) for re-assessment. If still sick on day 8, additional follow-up takes place after 2 weeks (day 15) and 1 month (day 29). To demonstrate that there is no significant increase in the percentage of children deteriorating clinically, the sample size needed for a noninferiority margin of 4%, a power of 80%, an alpha of 5%, and a design effect of 3 is 4284 children with unclassified fever. Main outcome is treatment failure on day 8, defined as death, hospitalization, one or more danger signs, or persistent fever.

**Results:**

The project was funded in 2015 and enrollment was completed 2016. Data analysis is currently under way, and the first results are expected to be submitted for publication in 2018.

**Conclusions:**

This study addresses the question as to whether there is any benefit in recommending universal follow-up among children seen for nonsevere unclassified fever, or whether parents can be counseled to return in the event of persistent fever, using a cluster randomized controlled trial design embedded in a national program. Outcomes will be relevant for policy makers and are important for the evaluation of current and future World Health Organization guidelines for the management of children with fever.

**Trial Registration:**

ClinicalTrials.gov NCT02926625; https://clinicaltrials.gov/ct2/show/NCT02926625 (Archived by WebCite at http://www.webcitation.org/6xrQWn50t)

## Introduction

### Burden of Disease in Children in Sub-Saharan Africa

Even though substantial progress has been made in reducing child mortality around the world, many countries did not achieve the Millennium Development Goal 4 [1]. For countries to reach the Sustainable Development Goals by 2030 [2], it is crucial that child health interventions focus on management of infectious diseases in children. Globally, mortality in children under 5 years stands at 43 per 1000 live births; it is estimated that 5.6 million children under 5 years die each year [3,4]. A large proportion of deaths are caused by infectious diseases such as pneumonia (15.5%), diarrhea (8.9%), and malaria (5.2%)—diseases with symptoms that overlap, making differential diagnosis difficult [5]. In response, many countries in sub-Saharan Africa have introduced integrated community case management (iCCM), where community health workers (CHWs) are trained to assess, classify, and treat uncomplicated cases of pneumonia, diarrhea, and malaria in children U5, and refer children with danger signs and malnutrition for facility-based care [6]. Although the mortality impact of iCCM has been difficult to demonstrate [7], there is clear evidence that it can increase the treatment rate among sick children [8].

### Control Strategies for Childhood Illnesses

In Ethiopia, the under-five mortality rate stands at 58 per 1000 live births; it is estimated that 187,000 children under 5 years died in the year 2016 [4,9]. As part of Ethiopia’s Health Extension Program, the Government has deployed over 42,000 female CHWs, or Health Extension Workers (HEWs) [10,11], to provide preventive, promotive, and curative health services at the community level; since 2010, iCCM has been scaled up in most regions of the country. There are typically 2 HEWs assigned to a health post in a sub-district with a population of 3000-5000. The HEWs are supervised by health centers that oversee approximately 5 health posts each. Medicines and supplies are distributed to the health posts by the Federal Ministry of Health, Regional Health Bureaus, and woreda (district) health offices, as well as by implementing partners. On the basis of surveys conducted in 2012, 90% of HEWs had all the essential iCCM drugs and supplies [12], and HEWs provided correct case management for 64% of children [13].

As per the World Health Organization’s iCCM guidelines [14], children diagnosed by a CHW with an illness are given treatment (on day 1) and counseled to return on day 3 to assess treatment compliance and illness resolution. Children with fever but without a diagnosable illness and without danger signs (ie, nonsevere unclassified fever) for whom treatment should be withheld are also told to return to the CHW on day 3, even if the child has recovered. This *universal* follow-up visit is either done through a return visit to the health post or through a home visit by the CHW.

### Unclassified Fever in Children

However, febrile illness is common in childhood, and is often due to viruses or other self-resolving illnesses [15,16]. In a large proportion of cases, fever resolves rapidly, almost always within 96 hours [17]. A number of studies have suggested that it is safe to withhold medical treatment for children with unclassified fever [18]. In Ethiopia, HEWs are instructed to follow the integrated management of neonatal and childhood illness (IMNCI) manual, which recommends that children seen by HEWs should only return for a re-assessment if the illness persists or deteriorates, that is, a *conditional* follow-up visit to the health post. However, HEWs and their supervisors report that a range of practices are applied for children with unclassified fever, including both conditional (as recommended) and universal follow-up advice, immediate referral to health centers, or treatment with antimalarial tablets, despite a negative malaria Rapid Diagnostic Test (mRDT).

There is limited evidence on which of the 2 follow-up recommendations (conditional as in IMNCI or universal as in iCCM) is safer for the child, and it is unclear whether caregivers of children actually come back promptly to the health post for their conditional follow-up visit if the child is not improving, or if they come back at all if the child in a universal follow-up situation has improved. Bacterial infections can develop quickly, and delaying care-seeking is a major risk factor for death in both pneumonia and malaria [19,20]; hence, children with untreated persistent fever may be at risk if caregivers do not comply with the conditional follow-up advice. A universal follow-up visit 2 days after an initial assessment for all children may promote detection of those at risk of developing severe illness. However, it could also potentially lead to delayed care-seeking for children whose health rapidly deteriorates at home if caregivers instead wait for their booked follow-up visit. In addition, the visit may add extra burden to families and HEWs and might be unnecessary if fever has resolved. On the caregiver side, opportunity costs and other barriers often hinder care-seeking for sick children, even when community-based providers are near and free of charge [21]. It is therefore unclear whether caregivers and HEWs would comply better with the conditional follow-up advice compared with the universal follow-up advice and whether the universal follow-up visit is even necessary.

This paper presents a protocol for a 2-arm cluster randomized controlled noninferiority trial conducted to assess whether conditional follow-up is noninferior to universal follow-up for nonsevere febrile illness in children U5, in whom malaria, pneumonia, diarrhea, or danger signs are absent.

## Methods

### Study Aim and Objectives

The study aims to assess the safety, in terms of the proportion of children whose health clinically deteriorates, of a follow-up visit conditional on nonresolution of symptoms for mRDT-negative children with no fast breathing, pneumonia, diarrhea, or danger signs, managed at the community level, compared with a universal visit for all these children on day 3.

#### Primary Objectives

The primary objective of the study was to assess the treatment failure after 1 week (on day 8), defined as the proportion of children with nonsevere unclassified fever who subsequently declined clinically (death, hospitalization, one or more danger signs, or persistent fever) subsequent to (1) conditional versus (2) universal follow-up of children under 5 years who present to HEWs with unclassified, nonsevere fever in 3 woredas (districts) in the Southern Nations, Nationalities and People’s Region (SNNPR) in southwest Ethiopia.

#### Secondary Objectives

The secondary objectives of this study were as follows:

To describe the clinical presentation and outcome of illness in those children whose symptoms do not resolve or where danger signs develop at day 8, to measure the rate of treatment failure at day 15 and 29 in both study arms for children who did not recover by day 8, and to determine the percentage of children who return for scheduled visits on day 3 (universal arm) or spontaneous visits before day 8 (universal and conditional arms).To determine the percentage of secondary treatment (antimicrobial medicines prescribed during visits to any providers after initial presentation to HEWs) in both study arms on day 8.To assess acceptability of the conditional or universal follow-up recommendations and no treatment with an antimicrobial to caretakers and HEWs, and determine why caretakers chose to return or not return to the HEW.

### Study Design

This is a 2-arm cluster randomized controlled trial (cRCT) carried out in 3 woredas in SNNPR in Ethiopia. Clusters defined by the health center (the lowest administrative unit where HEW services are coordinated) are randomized into either the *conditional* or *universal* follow-up arm. All children seeking care from the HEW health posts in these clusters are potential recipients of the interventions, in addition to having access to routine care available from private and public health services. Caregivers of children who meet the inclusion criteria (fever without malaria, pneumonia, diarrhea, or other symptoms requiring referral) are counseled to follow 1 of the 2 pathways, based on which intervention cluster the HEW belongs to. There are 25 clusters; 13 clusters in the universal follow-up arm and 12 in the conditional follow-up arm.

### Study Site

This research study will be conducted in 3 woredas , namely, Boloso Sore, Damot Gale, and Halaba in the Wolayita zone of SNNPR in southwest Ethiopia (see Figure 1). The iCCM program is functioning in all districts of SNNPR through support to the Regional Health Bureau from Save the Children International and the Integrated Family Health Program. It will therefore be an ideal environment to implement this research, as iCCM services are stable and the program is implemented by the Regional Health Bureau, which will provide technical oversight to this project.

According to the latest malaria indicator surveys, the rate of prompt care-seeking for fever is currently low, with only 46.3% of children under 5 years with fever taken for early treatment [22]. However, care-seeking at health post level shows an upward trend, presumably as a result of the increased awareness of the availability and proximity of child health services [12]. In addition, Malaria Consortium, with funding from the James Percy Foundation, has recently started implementing the Integrated Community-based Interventions for Malaria Services project in SNNPR. Activities include case detection by the volunteer Health Development Army who will work to ensure that all children with fever receive prompt diagnosis and treatment, and that children with danger signs get referred. As part of this grant, refresher training will also be provided to HEWs to negotiate optimal practices using behavior change communication tools and facilitation skills in community conversation. It is anticipated that these changes will lead to an increased use of HEWs in the study area.

The 3 woredas will be selected based on: (1) strength of iCCM program (ie, consistency in HEW supervision and supply), (2) HEW use rate among caregivers (≥50 children assessed for fever each month over a 12-month period), and (3) concurrent community mobilization activities under other grants (to ensure that demand was kept high during the study period). There are 25 health centers and 144 health posts with 284 HEWs in the 3 selected woredas.

### The Interventions

Children aged 2-59 months with fever (≥37.5 degrees Celsius) or a history of fever, a negative mRDT, no other symptoms of pneumonia or diarrhea, and no danger signs will be eligible to participate in the study. Figure 2 outlines the areas that consenting caregivers will be counseled on how to detect danger signs and seek care immediately from a health center if danger signs develop or the illness worsens; fever reduction strategies, such as tepid sponging and paracetamol; and that a study visit to assess clinical outcomes will take place after 1 week. Caregivers in the conditional arm will also be advised to return at any point to the HEW at the health post for re-assessment if symptoms persist or deteriorate (as per the Ethiopian IMNCI Guidelines), whereas caregivers in the conditional arm will be advised to return on day 3 to the HEW for a follow-up assessment, even if the child has recovered (as is common practice).

**Figure 1 figure1:**
[figure not shown]
Map of Ethiopia with the Southern Nations, Nationalities and People’s Region (SNNPR) and the three study woredas.

**Figure 2 figure2:**
[figure not shown]
Description of the 2 interventions arms, the current guidelines, and observed common practice. IMNCI: integrated management of neonatal and childhood illness.

At the day 3 re-assessment visit in the universal follow-up arm and at any spontaneous visit in both arms, the child will have a full re-assessment of their condition and the HEW will fill out a child assessment form. Caregivers will be asked whether the child remains febrile or whether the illness has resolved. If the child still has unclassified fever and a negative mRDT on re-assessment, the child will be referred to the nearest health center, as recommended in the national IMNCI guidelines. If the illness has resolved, the child will be sent home.

A clinically trained independent evaluator (IE) who is blinded to the study arm will visit all enrolled children at their home after 1 week to assess their clinical outcome. If caregivers report that the child is no longer ill and no fever is recorded, the child will be considered cured and no more follow-up will be done. If the caregiver reports that the child still has symptoms or if fever or other illness symptoms are detected during the assessment, the IE will follow the IMNCI algorithm and refer/treat the child accordingly. The IE will then follow-up again via a home visit after 2 weeks (day 15) and, if the child is still ill, on day 29.

At the day 8 visit, the IE will use a questionnaire to ask about individual and household characteristics, care-seeking and other treatments for the current illness episode, and reasons for returning/not returning to the HEW for follow-up care.

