### Outcomes

All enrolled children will have a study visit in their home with an IE after 1 week to assess their clinical outcome. Children who have not recovered on day 8 will be re-assessed after 2 weeks, and those whose illness persists on day 15 will be re-assessed on day 29. In addition, all enrolled children will be followed-up via a phone call for vital status on day 28. Management of illness at any follow-up visit (ie, return to HEW on any day; return to HEW for universal day 3 visit; or day 8, 15, and 29 assessment) will follow established national IMNCI guidelines.

The primary outcome is treatment failure on day 8, defined as the proportion of children with unclassified fever who subsequently declined clinically (death, hospitalization, one or more danger signs or persistent fever).

Secondary outcomes include:

Clinical presentation in those with unresolved illness at day 8 in each armTreatment failure on day 15 and 29, defined as the proportion of children with unclassified fever who subsequently declined clinically (death, hospitalization, one or more danger signs or persistent fever)Percentage of children who present to the HEW for the follow-up visit on day 3 in the universal follow-up armPercentage of children who spontaneously represent to HEW for persistence or worsening of symptoms in the conditional follow-up arm, and the timing of these visitsPercentage of children receiving secondary treatment (antimicrobial medicines prescribed during visits to any providers after initial presentation to HEW) in each arm between enrollment and day 8Caregiver and HEW acceptability of universal and conditional follow-up recommendations

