### Data Collection

HEWs will collect data using an Open Data Kit (ODK) [25] data collection form on mobile phones. Data will include date of enrollment, child identifiers, and clinical indicators (fever/axillary temperature, cough, respiratory rate, diarrhea, and danger signs). The enrollment data will be synchronized with a server which is accessed by a data manager who will download enrollments on a daily basis and schedule follow-up visits for 6 IEs using an online Google calendar.

The IEs will be equipped with tablets programmed with 3 ODK data collection forms; one for the day 8 visit, one for any extra visits (on day 15 or 29), and one vital status form for day 29. The data that will be collected during the household follow-up visits on day 8, 15, and 29 will include clinical data for the children following the IMNCI algorithm (eg, fever/axillary temperature, cough, respiratory rate, diarrhea, mid-upper arm circumference (MUAC) measure, and danger signs), any secondary treatment (antimicrobial medicines prescribed during visits to any providers after initial presentation to HEWs), hospitalization, care-seeking history, and costs, as well as caregiver and household characteristics. For children who cannot be found at home at the time of the home visit, 2 more attempts will be made over the 2 following days. After this, the child will be registered as a loss-to-follow-up for the primary outcome.

Moreover, 3 research assistants will enter data collected by HEWs for children who come back to the HEW spontaneously (universal and conditional arm) or on day 3 (universal arm) into an ODK sick child assessment form every 2 weeks.

A rigorous monitoring system will be implemented by the study team and will be part of the continuous quality assurance. The data manager will review forms submitted to the server daily and check for duplicates, completeness, and accuracy before storing them in the project database. Discrepancies, overdue follow-up visits, and other issues will be resolved by phone calls to the IEs and during weekly supervision meetings with field research staff. Biweekly field supervision visits to all HEWs will be carried out, and district HEW supervisors will be trained to monitor HEW trial activities during routine weekly group supervisions. A minimum of 10% of all enrolled cases and 50% of children with treatment failure will have a quality control re-assessment by a research assistant. The final dataset will be exported to STATA 13.

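### The day 8 evaluator is called blinded but also asks why the caregiver did or did not return to the HEW, so the blinding cannot be relied on

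*Protocol article*

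**What the plan says.** The blinding claim is in Methods, The Interventions, in the text that follows Figure 2: "A clinically trained independent evaluator (IE) who is blinded to the study arm will visit all enrolled children at their home after 1 week". In the same text, the same evaluator's day 8 questionnaire covers "care-seeking and other treatments for the current illness episode, and reasons for returning/not returning to the HEW for follow-up care".

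The arms differ in one thing, the advice about going back to the HEW. In one arm caregivers are "advised to return on day 3 to the HEW for a follow-up assessment, even if the child has recovered"; in the other they are to return only if the child does not improve. The sentence in The Interventions prints the word conditional for both arms, but the Introduction and the text after Figure 2 assign the day 3 visit to the universal arm, and I read it so.

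On allocation, Study Design says: "Clusters defined by the health center (the lowest administrative unit where HEW services are coordinated) are randomized". It adds: "There are 25 clusters; 13 clusters in the universal follow-up arm and 12 in the conditional follow-up arm". Under Data Collection, the data manager is to "schedule follow-up visits for 6 IEs using an online Google calendar".

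Under Outcomes, day 8 treatment failure is "death, hospitalization, one or more danger signs or persistent fever". Recovery is judged at the evaluator's visit: "If caregivers report that the child is no longer ill and no fever is recorded, the child will be considered cured".

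**The concern.** The questionnaire asks about the randomized intervention itself. A caregiver who explains that she was told to come on day 3 even if the child was well has stated the arm. Because the arm belongs to the health center, that answer also tells the evaluator the likely arm of every other child from the same center. Putting the questions after the examination would protect the child being examined, but not the children that evaluator sees there later.

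Part of the primary outcome passes through the evaluator's hands: asking about continuing illness, taking the temperature, judging danger signs. An evaluator who knows the arm could probe or judge differently by arm, and the noninferiority comparison would not show it. With a margin of 4 percentage points and an expected failure rate of about 5%, a small difference in ascertainment can matter.

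**Working it through.** **Inputs.** From Sample Size: 4900 children enrolled; 10% loss by day 8; 2142 per arm; design effect 3; failure 5% (universal) and 6% (conditional); margin 4 points; one-sided 5%; power 80%. From Study Design: 25 clusters. From Data Collection: 6 evaluators.

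**The plan's own figure.** n per arm = (1.645 + 0.842)² × (0.05 × 0.95 + 0.06 × 0.94) / (0.04 − 0.01)² = 714. Times 3 gives 2142 per arm and 4284 in total, as stated. The sample size is not affected by this point. The calculation fixes the effective size (714 per arm) for the illustration below.

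**How far knowledge of the arm could carry over.**
- Children per cluster: 4900 / 25 = 196. Children per evaluator: 4900 / 6 ≈ 817.
- Evaluator-by-cluster pairs: at most 6 × 25 = 150.
- If the first interview in each pair discloses the arm, later visits number 4900 − 150 = 4750, and 4750 / 4900 = 96.9%.
- With 10% lost by day 8, 4410 visits remain, and (4410 − 150) / 4410 = 96.6%.
- If five interviews per pair are needed (assumption): (4900 − 750) / 4900 = 84.7%. If ten (assumption): (4900 − 1500) / 4900 = 69.4%.
- If evaluators work by area there are fewer pairs and the share rises. With one evaluator per cluster and first-interview disclosure it is (4900 − 25) / 4900 = 99.5%.

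These are shares of visits made after disclosure. They are not shares of outcomes recorded wrongly.

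**What differential ascertainment could do (bias sizes assumed; none is in the document).** With 714 effective children per arm and the normal approximation, the chance of concluding noninferiority is Φ((0.04 − d)/SE − 1.645), where d is the recorded difference.

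| Share of conditional-arm failures missed (true rates 5% and 9%, at the margin) | Recorded conditional rate | False noninferiority |
|---|---|---|
| 0% | 9.0% | 5.0% |
| 5% | 8.55% | 9.6% |
| 10% | 8.1% | 16.9% |
| 20% | 7.2% | 41.2% |

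In the other direction, with true rates of 5% and 6%, over-calling conditional-arm failures by 10% or 20% lowers power from 80% to 61.7% or 41.2%.

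**The case against.** Much of the case on the other side stands.

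- **Not every answer discloses the arm.** That the child got better, or was still ill, fits either arm, and spontaneous returns are expected in both. The Introduction reports that HEWs have in practice given both kinds of advice, and Data Analyses allows for advice that does not match the arm. A single answer is an imperfect signal, and only the evaluator who heard it has it unless it is shared. A reader might infer that one answer unblinds every later assessment in the cluster; the document does not support that.
- **Exposure is not bias.** A reader might infer from the 97% that most outcomes are biased, or that the trial is tilted toward noninferiority. Neither follows. The 97% assumes disclosure at the first interview, and nothing in the document gives a direction or size.
- **Parts of the outcome are firm.** Death and admission are largely factual, temperature is measured, and danger signs follow the IMNCI algorithm.
- **There is a re-assessment.** Data Collection plans quality control re-assessment of at least 10% of cases and 50% of treatment failures. This is only a partial check: no blinding is stated for it, and it falls to research assistants, a role that also enters the HEW day 3 and spontaneous-visit forms.
- **The article is condensed.** Question order, masking of the cluster and evaluator briefing may be in the full protocol, and their absence is no finding. What remains is that the article itself states both the blinding and the duty that undermines it. Question order alone would not repair this for later children.

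**Conclusion.** The point holds in a limited form. The article claims evaluator blinding that its own day 8 visit cannot be relied on to preserve, because the evaluator asks about the one thing that separates the arms and the arm is shared across a cluster of about 196 children. An informative answer is likely early in most evaluator-by-cluster pairs. On that reasoning roughly 69% to 97% of assessments would follow disclosure if between ten and one interviews per pair were needed, with all 150 pairs in use; those interview counts are assumptions. Persistent fever and danger signs are the components most open to influence. Direction and size of bias are unknown, so this is a reason to change the procedure and qualify the claim. It is not evidence that the result is wrong.

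**What to change.** 1. In the day 8 ODK form, record and lock temperature, danger signs, reported illness and admission before any care-seeking item opens.
2. Take the return and advice items off the evaluator's form. Whether and when the child returned can come from the HEW forms that the research assistants already enter. Reported advice and reasons should be collected by staff who do not assess outcomes. The planned vital status contact is not a ready substitute, because that form sits on the evaluators' own tablets. Collect these items soon after day 8: Data Analyses uses reported advice to define the per-protocol set, so late recall or failed contacts would change who is in the main analysis.
3. Report measured temperature of 37.5 or above, and death or admission, as separate sensitivity outcomes.
4. The remaining care-seeking items are needed for the secondary-treatment outcome and can still hint at the arm. For that reason, and because enrollment was completed in 2016 so that data already collected cannot be re-gathered, describe the evaluators as not reliably blinded. For this trial, items 3 and 4 are what can still be done.

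Cost: re-ordering one form, some extra contact work for existing staff, and some recall error or missing data on the advice items. Items 3 and 4 need only reporting.
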